## Abstract

**Introduction:**

Exposure to SARS-CoV-2 during pregnancy or in the neonatal period may impact fetal or neonatal brain development either through direct central nervous system infection or indirectly through the adverse effects of viral infection-related inflammation in the mother or newborn infant. This study aims to determine whether there are early neurodevelopmental effects of SARS-CoV-2 infection.

**Methods and analysis:**

We will conduct a prospective national population-based cohort study of children aged 21–24 months who were born at term (≥37 weeks’ gestation) between 1 March 2020 and 28 February 2021 and were either antenatally exposed, neonatally exposed or unexposed (comparison cohort) to SARS-CoV-2. Nationally, hospitals will identify and approach parents of children eligible for inclusion in the antenatally and neonatally exposed cohorts using information from the UK Obstetric Surveillance System (UKOSS) and British Paediatric Surveillance Unit (BPSU) national surveillance studies and will identify and approach eligible children for the comparison cohort through routine birth records. Parents will be asked to complete questionnaires to assess their child’s development at 21–24 months of age. Outcome measures comprise the Ages and Stages Questionnaire, Third Edition (ASQ-3), Ages and Stages Questionnaire Social-Emotional, Second Edition (ASQ-SE-2), Liverpool respiratory symptoms questionnaire and questionnaire items to elicit information about healthcare usage. With parental consent, study data will be linked to routine health and education records for future follow-up. Regression models will compare ASQ-3 and ASQ-SE-2 scores and proportions, frequency of respiratory symptoms and healthcare usage between the exposed and comparison cohorts, adjusting for potential confounders.

**Ethics and dissemination:**

Ethics approval was obtained from the London-Westminster Research Ethics Committee. Findings will be disseminated in scientific conference presentations and peer-reviewed publications.

**ISRCTN registration number:**

ISRCTN99910769.

WHAT IS ALREADY KNOWN ON THIS TOPICThe incidence of vertical transmission of SARS-CoV-2, as well as the incidence of SARS-CoV-2 infection in neonates is low.Most neonates infected by SARS-CoV-2 had mild symptoms or were asymptomatic.SARS-CoV-2 has neuroinvasive potential and may impact children’s neurodevelopment.WHAT THIS STUDY ADDSA population-based evaluation of the impact of SARS-CoV-2 infection in pregnancy or in the neonatal period on children’s neurodevelopment at 21–24 months of age.An assessment of healthcare usage and respiratory symptoms in children exposed to SARS-CoV-2 infection as a fetus or neonate compared with non-exposed children.HOW THIS STUDY MIGHT AFFECT RESEARCH, PRACTICE AND/OR POLICYThe outcomes of this study will inform public health advice provided by the National Health Service and clinicians to pregnant women and parents of newborn babies exposed to SARS-CoV-2 infection.

## Introduction

The SARS-CoV-2 virus has infected over 300 million people worldwide.^1^ Changes occurring to the immune system during pregnancy may predispose pregnant women to SARS-CoV-2 infection,^2^ and pregnant women with SARS-CoV-2 infection are at increased risk of requiring critical care.^3 4^ In a previous study, 95% of babies born to women with confirmed SARS-CoV-2 during pregnancy did not have a confirmed SARS-CoV-2 infection in the neonatal period.^3^ Where babies were infected in the neonatal period, possible transmission occurred from the mother in 26%, but this was most commonly in the postnatal period and vertical transmission appears to be rare.^5^ Overall the incidence of SARS-CoV-2 infection in neonates is low (5.6 per 10 000 live births),^5^ and most neonates had mild symptoms or were asymptomatic.^6^ However, the long-term outcomes for these infants are unknown.

There are various possible mechanisms through which SARS-CoV-2 infection may adversely impact the developing fetus. SARS-CoV-2 infection triggers inflammation^7^ which can pass through the placenta and may impact fetal brain development.^8^ Severe SARS-CoV-2 infection requiring critical care, which is more common in pregnancy, may impair uteroplacental blood flow inducing ischaemic brain injury to the fetus.^9^ SARS-CoV-2 may directly affect the fetal brain, as the placenta expresses the ACE-2 receptor for SARS-CoV-2,^10^
^11^ and SARS-CoV-2 has been detected in placental tissue^11–13^ and amniotic fluid.^14^ Transplacental transmission has also been accompanied with neurological symptoms.^13 15^ However, based on the criteria for probable or possible intrapartum acquired neonatal SARS-CoV-2 infection,^16^ only 3% of hospitalised neonates were considered to have possible vertical transmission.^5^

SARS-CoV-2 has been associated with increased incidence of neurological and cognitive deficits in adults.^17 18^ In adults with confirmed SARS-CoV-2 infection, SARS-CoV-2 RNA has been detected in brain tissue,^19^ and neuroimaging abnormalities have been observed in brain regions functionally connected to the human olfactory system.^20 21^ Neuroimaging abnormalities have also been detected in white matter in an infant,^15^ and acute disseminated encephalomyelitis-like changes have been observed in the brains of children with acute and subacute SARS-CoV-2 infection.^22^ SARS-CoV-2 also evokes a widespread hyperinflammatory state with a ‘cytokine storm’ in some severely affected individuals,^7^ and severe disease is well described in pregnancy.^3 4^ In utero or early life exposure to high levels of inflammation^23 24^ is known to be associated with cerebral white matter damage, leading to neurodevelopmental disorders in childhood and a range of long-term disabilities.^25^ Taken together, this suggests SARS-CoV-2 exposure in a fetus or neonate has the potential to adversely affect long-term neurodevelopment, either directly or indirectly via the effect of inflammation accompanying SARS-CoV-2 infection on the developing brain.

In the UK in March to April 2020, the majority of pregnant women who were hospitalised with SARS-CoV-2 were admitted in the late second or third trimester^3^ and 73% gave birth at 37 weeks’ gestation or later.^5^ Among neonatal cases of SARS-CoV-2 infection, two-thirds occurred in term-born babies.^5^ Enhanced developmental surveillance is recommended for preterm but not term-born infants; therefore, there is an urgent need to investigate the potential impact of antenatal or neonatal SARS-CoV-2 exposure on neurodevelopment in term-born infants. Given that SARS-CoV-2 infection impacts the respiratory system during acute infection in both neonates and adults,^5 26^ there may also be a long-term effect on lung function and consequently healthcare usage. Therefore, in addition to assessing neurodevelopment, we intend to establish whether there are any long-term impacts on respiratory function and healthcare usage.

### Study aims and objectives

This study aims to investigate neurodevelopmental effects of SARS-CoV-2 infection.

The primary objective of the study is to investigate the impact of antenatal and neonatal exposure to SARS-CoV-2 on infants’ global development at 21–24 months of age.

The secondary objectives are to assess the impact of antenatal and neonatal SARS-CoV-2 exposure on:

Infants’ cognitive, fine motor, gross motor, communication and social-emotional development at 21–24 months of age.Infants’ respiratory symptoms at 21–24 months of age, and infant’s utilisation of healthcare services.

## Methods

### Study design

A prospective national population-based cohort study of children aged 21–24 months with (exposed cohort) and without (comparison cohort) antenatal or neonatal exposure to SARS-CoV-2, who were born at term between 1 March 2020 and 28 February 2021.

The antenatal exposure cohort will include infants born to women with confirmed SARS-CoV-2 infection during pregnancy and will be identified from the UKOSS COVID-19 in pregnancy study.^3^ The neonatal exposure cohort will include infants with confirmed SARS-CoV-2 infection as a neonate and will be identified from the BPSU Neonatal Complications of Coronavirus Disease study.^5^ These studies reported ongoing nationwide hospitalisation of pregnant women and neonates with SARS-CoV-2 infection, respectively. The comparison cohort will include infants born to women without evidence of SARS-CoV-2 infection during pregnancy, and whose baby did not have confirmed SARS-CoV-2 infection as a neonate, and these infants will be identified at the same hospitals that reported cases of maternal SARS-CoV-2 infection in pregnancy through the UKOSS study.

### Inclusion criteria

Antenatal exposure cohort includes term-born (≥37 weeks’ gestation) singleton infants of mothers hospitalised with confirmed SARS-CoV-2 infection in pregnancy between 14 and 36+6 weeks’ gestation.Neonatal exposure cohort includes term-born singleton infants with confirmed SARS-CoV-2 infection who were hospitalised in the first 28 days after birth.Comparison cohort includes term-born singleton infants born during the same period as the exposed cohorts, and with no evidence of maternal SARS-CoV-2 infection in pregnancy or neonatal SARS-CoV-2 infection.

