### Exclusion criteria

Children born preterm.Children with a major congenital anomaly.Children born following multiple pregnancy.Children who have left the UK.

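### Neonatal cohort entry allows maternal infection in pregnancy while the comparison cohort bars it, so the neonatal contrast can mix antenatal with neonatal exposure

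*Protocol article*

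**What the plan says.** The Protocol article, under Inclusion criteria, defines three cohorts of term-born singletons.

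- Antenatal exposure, by the mother's infection alone: "infants of mothers hospitalised with confirmed SARS-CoV-2 infection in pregnancy between 14 and 36+6 weeks" of gestation. The infant's own infection status is not mentioned.
- Neonatal exposure, by the infant's infection and hospital stay alone: "Neonatal exposure cohort includes term-born singleton infants with confirmed SARS-CoV-2 infection who were hospitalised in the first 28 days after birth". The mother's status in pregnancy is not mentioned.
- Comparison, by the absence of both: children "with no evidence of maternal SARS-CoV-2 infection in pregnancy or neonatal SARS-CoV-2 infection".

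The Exclusion criteria, "Children born preterm.Children with a major congenital anomaly.Children born following multiple pregnancy.Children who have left the UK", do not touch dual exposure.

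Under Study design, the two exposed cohorts come from separate registers. The antenatal cohort "will be identified from the UKOSS COVID-19 in pregnancy study", and the neonatal cohort "will be identified from the BPSU Neonatal Complications of Coronavirus Disease study". No section says where a child who appears on both belongs.

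The Data analysis section compares the exposed cohorts with the comparison cohort by regression. Its confounders are given as examples (ethnicity, sex, socioeconomic status), and its sensitivity analysis concerns conditions other than SARS-CoV-2.

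**The concern.** Maternal infection in pregnancy comes before neonatal infection, can lead to it, and is itself suspected of harming development. For the neonatal contrast it is therefore a confounder. The eligibility text removes it from the comparison side and leaves it on the neonatal side, so any antenatal effect carried by dual-exposed children is credited to neonatal infection.

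The gap is wider than the overlap of the two registers. A neonatal case whose mother was infected before 14 weeks, from 37 weeks onward, or without being hospitalised enters the neonatal cohort. An uninfected infant of that same mother would fit neither the antenatal nor the comparison cohort.

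The stake is attribution. The article names both exposures in its primary objective, sizes each exposed group separately, and intends the results to inform advice both to pregnant women and to parents of newborns. A neonatal estimate that is partly antenatal serves neither audience well.

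**Working it through.** **Scale, from the Sample size section.** SD of ASQ-3 total = 50.84; target difference 0.5 SD; alpha 0.05 (taken as two-sided); power 90%.

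n per group = 2 × (1.960 + 1.282)² / 0.5² = 2 × 10.51 / 0.25 = 84.1, rounded up to 85. The stated 85 reproduces (the t-test version gives 85.03). The sample size is not in dispute; it only supplies the SD and effect size used below.

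**What the documents say about overlap (Introduction).**

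- Among infected neonates, "possible transmission occurred from the mother in 26" per cent. The sentence goes on to say that this was mostly postnatal.
- Possible vertical transmission was 3% of hospitalised neonates.
- "95% of babies born to women with confirmed SARS-CoV-2 during pregnancy did not have a confirmed SARS-CoV-2 infection in the neonatal period", so about 5% did.

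Neither 26% nor 3% measures the share of neonatal cases whose mothers were infected in pregnancy. That share, f, is therefore an assumption. The two figures are used only to span a range, with 10% as an arbitrary midpoint.

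**Shift in the neonatal estimate.** Suppose neonatal infection has no effect and antenatal exposure lowers the score by 0.5 SD. Then shift = f × 0.5 SD, and points = shift × 50.84. The last column is the chance of a significant neonatal result at a nominal 5%, with 120 neonatal and 200 comparison children.

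| f | Shift (SD) | Points | Chance of significance |
|---|---|---|---|
| 3% | 0.015 | 0.8 | 5.2% |
| 10% | 0.05 | 2.5 | 7.2% |
| 26% | 0.13 | 6.6 | 20% |

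**Cost of removing dual-exposed children from the neonatal contrast.** If all 120 eligible children enrol, 120 × (1 − f) leaves 116, 108 or 89. Power for 0.5 SD against 200 comparison children is 0.99, 0.99 or 0.97. If only 85 enrol, 82, 76 or 63 complete cases remain (85 × (1 − f), rounded down after the decimal except for 62.9), with power 0.97, 0.96 or 0.93.

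In SD units the standard error, with 120 enrolled, goes from √(1/120 + 1/200) = 0.115 to √(1/116.4 + 1/200) = 0.117 at 3%, and to √(1/88.8 + 1/200) = 0.128 at 26%. That is an increase of about 1% to 10%.

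**The other direction.** If 5% of the antenatal cohort had neonatal infection with its own 0.5 SD effect, the antenatal estimate would move by 0.05 × 0.5 = 0.025 SD, or 0.025 × 50.84 = 1.3 points.

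**The case against.** The strongest reply is that a condensed article may leave the handling of dual-exposed children to the full protocol or analysis plan. The confounder list is only illustrative, and SARS-CoV-2 infection status is collected at study entry. So a reader should not infer that the analysis ignores dual exposure; the article does not say that. This part of the reply stands. It does not dispose of the point, because eligibility is stated here, and as stated it bars maternal infection from one side of the contrast only.

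Three stronger readings are tempting and are not supported.

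- *The background figures prove a sizeable overlap.* They do not. The 26% is mostly transmission after birth, which fits the neonatal definition without any antenatal exposure. Applying 5% to the roughly 830 eligible antenatal children gives 41.5, or 35% of 120. But the 5% covers all babies of infected women, whereas the antenatal cohort requires infection by 36+6 weeks and birth at term, and the neonatal cohort requires hospitalisation. It is a loose ceiling, not an estimate.
- *Children will be counted twice.* The text leaves this open but does not state it. The Recruitment section provides one study pack per eligible child, which makes double enrolment less likely, though it does not settle which contrast the child enters.
- *Both contrasts should be restricted to singly exposed children.* For the antenatal contrast this is unsound as a primary rule. Neonatal infection may be a consequence of antenatal exposure, so removing those infants discards part of the effect under study.

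It is also fair to say that 0.5 SD is the difference the study is sized to detect, not an expected antenatal effect.

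**Conclusion.** The point holds for the neonatal contrast. The two exposed cohorts are not mutually exclusive, maternal infection in pregnancy is allowed among neonatal cases and excluded from comparison children, and the article gives no rule for a child on both registers.

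The size is uncertain and may be small. The 0.8 to 6.6 point range rests on an assumed overlap of 3% to 26% and an assumed additive antenatal effect of 0.5 SD. Given that transmission from the mother was mostly postnatal and vertical transmission is described as rare, the true shift may be near the low end, where the false-positive rate barely moves. The reason to act is that the ambiguity concerns what the neonatal estimate means, and it can be removed cheaply with information the study already plans to hold.

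**What to change.** 1. Classify every exposed child as antenatal only, neonatal only or both, using the surveillance records and the infection status from the entry questionnaire. For this purpose count any evidence of maternal infection in pregnancy, not only hospitalised infection at 14 to 36+6 weeks. Report the number with both, and state which cohort takes a child found on both registers.
2. Estimate the primary neonatal contrast in children with no evidence of maternal infection in pregnancy, or adjust for it. Show it again with the dual-exposed children added back.
3. Keep dual-exposed children who meet the antenatal definition in the primary antenatal contrast. Exclude them only in a sensitivity analysis.

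The cost is wording in the cohort definitions and the analysis, with no new data collection. The downside is slightly lower precision in the already small neonatal group, which is why the add-back analysis is worth reporting.

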### Exclusion criteria

Children born preterm.Children with a major congenital anomaly.Children born following multiple pregnancy.Children who have left the UK.

### Recruitment

The parents of eligible children will be approached and recruited through the hospitals that cared for the mother or child during SARS-CoV-2 infection or during birth. The study coordinator based at the National Perinatal Epidemiology Unit at the University of Oxford will send study information packs to the hospitals, where one study pack will be dispatched to the parent of each eligible child. The study information packs include:

Study invitation letter to parents of the eligible children.Parent information sheet.Form providing information in seven non-English languages (Arabic, Gujarati, Hindi, Polish, Punjabi, Somali and Urdu) on how to find out more about the study in different languages.Informed consent form.Non-participation form.Study entry questionnaire.Freepost return envelope.

The local hospital research teams will be provided with the UKOSS ID for the mothers of antenatal exposure cohort participants and the BPSU ID, National Health Service (NHS) number and date of birth of the neonatal exposure cohort participants. The hospital research teams will use these details to identify the names and addresses of the mothers and eligible children in the antenatal and neonatal exposure cohorts, respectively, from locally held information. The hospital research teams will also identify up to four babies (depending on current recruitment rates) who met the comparison cohort eligibility criteria and were born around the same time as each child with antenatal exposure using routine birth records—two babies born before and two babies born after the antenatal exposure baby, preferably on the same day. The hospital teams will also have the option to telephone the parents of eligible children and inform them about the study prior to posting each parent a study information pack.

### Informed consent

Parents will be able to enrol their children onto the study by completing the consent form and study entry questionnaire and returning these forms to the central research team at the University of Bristol using the freepost return envelope. Parents who do not want to be involved in the study will be able to indicate this by returning the non-participation form. Parents will also be able to complete these forms online by following a weblink provided in the invitation letter. Parents who do not return any forms after 3 weeks will be sent one reminder study pack.

In addition to seeking parental consent for the child to take part in the study, the informed consent form will request consent to (1) retain the contact details of the parents to allow the research team to contact them to be invited to participate in future follow-up assessments, (2) link the child’s study data to records held by the Department for Education on academic attainment and special education needs (in the National Pupil Database) and (3) link the child’s identifier to NHS Digital records (Hospital Episode Statistics and primary care attendance data).

### Procedures and data collection

Data will be collected through parent-completed questionnaires, either by parents returning paper copies to the central research team by post or by completing the questionnaires online using a secure weblink or over the phone with the study researcher.

Parents will complete the study entry questionnaire when providing informed written consent. This questionnaire will collect information about:

Parents’ preferred choice of completing questionnaires (ie, online or via post or phone).The need to use translation services.Demographic characteristics.SARS-CoV-2 infection status.Information on other conditions that might impact neurodevelopment.

Parents will then be sent data collection materials when their child reaches 21–23 months of age. These will consist of the following questionnaires:

The Ages and Stages Questionnaire, Third Edition (ASQ-3) 22-month questionnaire^27^ in English, a widely used developmental screening tool to identify children at risk of developmental delay.^28^ The ASQ-3 assesses development in five domains: fine motor, gross motor, communication, personal-social functioning and problem-solving.The Ages and Stages Questionnaire: Social-Emotional, Second Edition (ASQ-SE-2) 24-month questionnaire^29^ in English, a widely used measure to identify children at risk of social-emotional problems.^30^Liverpool Respiratory Symptoms Questionnaire (LRSQ), developed to assess patterns of wheezing and other respiratory symptoms in infants and preschool children.^31^A non-validated questionnaire collecting information about the use of healthcare services and personal financial costs (online supplemental appendix 1).

10.1136/bmjpo-2022-001571.supp1Supplementary data

We chose the ASQ-3 and ASQ-SE-2 as they are validated parent-completed questionnaires that are widely used to identify children at risk of development delay in multiple domains.^28^ Questionnaires will be completed over the telephone with the assistance of an interpreter for families who do not speak or read English sufficiently to complete the English version of the questionnaires. Parents who do not return the questionnaires within 2 weeks will be sent a reminder email or text message, and if there is no response after a month, parents will be contacted again. Parents who do not respond to invitations to complete the ASQ-3 before their child reaches 23 months old will be sent the subsequent age band ASQ-3 24-month or 27-month questionnaire. Parents will be informed of the results of their child’s ASQ questionnaire results after completion. If the questionnaires highlight possible developmental delay according to standardised cut-offs, parents will be advised to contact their health visitor and/or general practitioner for further assessment.

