### Outcome measures

The primary outcome measure for this study is the mean total ASQ-3 score, and the secondary outcomes are the following:

Proportion with one or more ASQ-3 domain scores below the established cut-offs which identify possible developmental delay.Proportion of ASQ-3 domain scores below the established cut-offs which identify possible developmental delay.Mean ASQ-SE-2 total score and proportion of ASQ-SE-2 total scores above the established cut-offs which identify possible developmental delay.Mean LRSQ total score.Frequency of healthcare usage.

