### Sample size

The study sample size aims to be able to detect a difference in neurodevelopment associated with perinatal SARS-CoV-2 exposure of similar magnitude to that seen in term-born infants with mild neonatal encephalopathy: a difference in developmental score of 6 points (0.5 SD).^32^ Therefore, to detect a similarly clinically meaningful between-group difference of 0.5 SD in mean ASQ-3 total score (mean (SD) 203.02 (50.84))^33^ in exposed versus comparison infants, with a type-I error of 0.05 and 90% power, we will need a minimum of 85 infants in each of the two exposure groups and in the comparison group.

To achieve a sufficient sample size for future follow-up studies at school-age considering potential attrition, we aim to recruit at least 200 children in each group. Given the 20% response rate in a previous study of similar design using the UKOSS platform,^34^ we will approach the parents of up to 1000 children in the antenatal exposure cohort (currently there are around 830 eligible antenatal exposure cohort children) and up to 2000 families for the comparison cohort, as we expect response rates to be lower for the comparison cohort. Given that there are around 120 eligible children in the neonatal exposure cohort to date, we will approach the parents of all these infants. Consequently, our target sample size comprises 200 children in the antenatal exposure cohort, 200 in the comparison cohort and up to 120 children in the neonatal exposure cohort.

Patient and public involvement

The study design was discussed with a patient and public involvement (PPI) group consisting of a parent of an infant exposed to SARS-CoV-2 in the antenatal period and another parent whose infant was exposed to SARS-CoV-2 in the neonatal period. The PPI group agreed that the research question is important and the design and outcomes to be measured are appropriate. The parent information sheet and consent form were developed with input from the PPI group, and further PPI will be sought to support the conduct of the study and help with interpreting the results.

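### The late-responder rule allows ASQ-3 forms beyond the stated 21–24 month window and feeds up to three age-specific forms into one primary mean total score, with no stated handling of form or age

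*Protocol article*

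**What the plan says.** All of this is in the protocol article.

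- **Age window.** The primary objective (Study aims and objectives) concerns "global development at 21–24 months of age". The abstract and the Study design section use the same window.
- **Default form and timing (Procedures and data collection).** The default instrument is "The Ages and Stages Questionnaire, Third Edition (ASQ-3) 22-month questionnaire". On timing: "Parents will then be sent data collection materials when their child reaches 21–23 months of age".
- **Late-responder rule (same section).** Parents who have not responded before the child is 23 months old "will be sent the subsequent age band ASQ-3 24-month or 27-month questionnaire". No age is given after which a questionnaire is no longer accepted.
- **Primary outcome (Outcome measures).** "The primary outcome measure for this study is the mean total ASQ-3 score". The text does not say how totals from different forms are combined.
- **Planning values (Sample size).** One mean and SD for the total score, 203.02 (50.84), and a target difference of 0.5 SD.
- **Adjustment (Data analysis).** Multiple linear regression for continuous outcomes. Ethnicity, sex and socioeconomic status are given as examples of confounders in an open list. Neither questionnaire form nor age at completion is named.

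**The concern.** There are two linked problems.

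The first is a contradiction. The objective is tied to 21–24 months, yet the data-collection rule allows the age band that follows the 24-month form. A child assessed on the 27-month form does not contribute an outcome at the stated age.

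The second concerns what the primary score measures. The article itself treats the forms as age-specific, since it calls them age bands and switches between them by the child's age. It then defines one mean total score. The same total on two forms need not mean the same level of development. Form is decided by how quickly a parent replies, not by design. If slow reply is more common in one cohort, a difference in form mix could appear as a developmental difference or mask a real one. A larger sample does not remove that bias.

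The binary ASQ-3 outcomes are less exposed, because they rest on established cut-offs. The continuous primary outcome has no such protection in the text.

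**Working it through.** **1. The plan's own figure.** Target difference: 0.5 × 50.84 = 25.42 points. With two-sided alpha 0.05, 90% power and equal groups, n per group = 2 × (1.960 + 1.282)² / 0.5² ≈ 84.1, rounded up to 85. This matches the stated minimum of 85. Power at 85 per group is 90.3% (normal approximation) or 90.0% (t-test). The sample size is not in question. It shows that planning used one total-score scale.

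**2. The age window against the rule.** Materials may go out as late as 23 months. The same section allows a further contact if there is no reply after a month, so for such a child that contact comes at 23 + 1 = 24 months at the earliest, the end of the stated window. The later forms are sent once 23 months has passed without a reply. The 27-month form is the band after the 24-month one, and no cut-off age is given. The rule and the window cannot both stand as written.

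**3. Size of a possible bias.** For two cohorts,

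bias = (mean shift in total between forms) × (difference between cohorts in the share using the later form).

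The documents give neither input. Assumed ranges are a shift of 10–25 points and a share difference of 10–30 percentage points.

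- Lower end: 10 × 0.10 = 1.0 point; 1.0/50.84 = 0.02 SD; 1.0/25.42 = 4% of target.
- Upper end: 25 × 0.30 = 7.5 points; 7.5/50.84 = 0.15 SD; 7.5/25.42 = 30% of target.
- Equal late shares: bias = 0, whatever the shift.

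**4. Effect on error rates.** SE = 50.84 × √(1/n₁ + 1/n₂), which is 7.80 at 85 v 85, 5.08 at 200 v 200 and 5.87 at 120 v 200. The false-positive rate is that of a nominal 5% two-sided test when the true cohort difference is zero. Power is for a true 25.42-point difference that the bias partly masks. The last row uses a shift equal to the whole target difference, 25.42 points, as an extreme.

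| Assumed shift | Late-share difference | Bias (points) | False-positive rate: 85 v 85 / 200 v 200 / 120 v 200 | Power at 85 / 200 per group |
|---|---|---|---|---|
| any | 0 | 0 | 5% / 5% / 5% | 90.3% / 99.9% |
| 10 | 10 pp | 1.0 | 5.2% / 5.4% / 5.3% | 87.9% / 99.8% |
| 10 | 20 pp | 2.0 | 5.8% / 6.8% / 6.3% | 85.2% / 99.6% |
| 15 | 30 pp | 4.5 | 8.9% / 14.3% / 12.0% | 76.5% / 98.4% |
| 25.42 | 30 pp | 7.6 | 16.5% / 32.3% / 25.5% | 62.6% / 93.8% |

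Under moderate inputs (10 points, 20 percentage points) the bias is 0.04 SD, or 8% of the target. Only the extreme row distorts the error rates badly.

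**The case against.** The strongest reply is that the contradiction over age is real but the bias is conditional, and that handling of form may sit in an analysis plan or full protocol not shown here. Much of this stands, and it rules out several stronger readings.

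- **That the plan expects late return to differ by cohort.** A reader might infer this from the Sample size section, which approaches more comparison families "as we expect response rates to be lower for the comparison cohort". That remark concerns uptake of the study invitation. The late-form rule applies later, to families sent the developmental questionnaires. Lower uptake makes different lateness plausible but does not show it.
- **That raw totals are pooled without adjustment.** One mean total score planned on one SD suggests a single average across forms, but the article never says totals are raw or unadjusted, and its confounder list is open.
- **That the forms give different mean totals.** No form-specific means or SDs are given. Matching the form to the child's age may itself offset part of the age effect.
- **That out-of-window children should leave the primary analysis.** That would select on response. It would also shrink the neonatal cohort, which has at most about 120 eligible children against a stated minimum of 85.

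What the reply does not meet is that the window and the late-responder rule are both protocol content and disagree. The rule itself produces mixed-form data for the primary outcome, so this is more than a detail left to another document.

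**Conclusion.** The point holds in two parts. First, the 21–24 month window conflicts with a rule that allows the 27-month form and states no upper age limit. This needs no assumption. Second, age-specific forms feed one primary score with no stated treatment of form or age, which leaves the cohort contrast open to bias. That bias needs both a shift between forms and unequal late shares. On the assumed ranges it is 1–7.5 points (0.02–0.15 SD), small in the moderate cases and zero if late shares are equal. The documents do not establish that the bias exists, in which direction it would run, or that it would overturn the primary result. The change is worth making because it protects the primary contrast at almost no cost.

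**What to change.** 1. Add questionnaire form and exact age at completion to the linear model already planned for the primary outcome. Alternatively, standardise each total within form against that form's reference mean and SD, and analyse the standardised score.
2. Reconcile the assessment window with the late-responder rule, either by amending the stated window or by stating an upper age limit.
3. Keep all forms in the primary analysis, and add a sensitivity analysis limited to assessments completed at 21–24 months.

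The cost is a little more analysis work and, if the window is amended, a slightly wider stated age range. Form and completion date must be held for each child, which the article does not say. Standardising needs reference values for each form, which the article does not give. The sample size does not change.
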